### Dissemination

The results of our research will be disseminated through presentations at regional and national audiology conferences. The study outcomes will be published through peer-reviewed journals. There is no limit in the publication of the trial results.

### Monitoring

Eight independent audiology experts who are the academic members of rehabilitation schools in Shahid Beheshti University of Medical Sciences (SBMU) and Iran University of Medical Sciences (IUMS) will monitor patient safety and treatment efficacy. They approved the relevance, clarity and simplicity material of the study.

## Study status

The enrolment of the patients has been performed and the allocation will be performed in the near future. The study started in November 2019 and will continue until December 2020.

## Discussion

Elderly populations are growing rapidly worldwide, and this higher number of older individuals is associated with an increase in prevalence and incidence of age-related disorders. Age-related hearing loss (presbycusis) is one the most common disorders with an increase in age. Hearing loss has significant negative impact in quality of life in elderly population. It causes limitation of communication and social activity
^1^.

Speech perception in noisy environments is very serious difficulty with presbycusis, The presbycusis is known as damage of hair cells in cochlea
^5^. The hair cells damage with presbycusis mostly associated with deteriorate of temporal fine structure (TFS) information
^7^.

TFS is important when background sounds are present
^9^. Loss of speech perception in noisy environments with presbycusis is mostly caused by damage of processing of TFS information. Our study is based on improvment of TFS deficit in cochlea.

The rehabilitation training is based on identify vowel consonant vowel words (VCV). 

The test is performed in several sessions. The total time of test is three times every week for total fives week for all subjects but the time in every session is different between participants.

To evaluate the efficiency of rehabilitation training we used temporal fine structure sensitivity test (TFS test), Speech in noise test (SNR 50%) and Speech, Spatial and Qualities of Hearing Scale (SSQ) 

They are performed in both intervention and control group but at the end of study we measure only the tests in intervention population.

Initially TFS1 was developed by Moore and Sek (2009) in order to discriminate a harmonic complex tone from the same tones with all components shifted upwards by the same amount in hertz leading to an inharmonic tone. The TFS-LF was described by Moore and Hopkins (2010) to measuring thresholds for detecting changes in interaural phase difference ( IPD). Although the TFS-LF is used generally but it has a limitation. The frequency of the tones is fixed, for example at 250, 500 or 750 Hz and some old
listener have difficulty to perform the test with chosen frequency. This limitation led to develop TFS-AF test. In TFS-AF test IPD is fixed for example is 180 degree with frequency adaptively varied to determine a threshold. In this study, we used TFS-LF test in all participants because TFS-LF test provides a good measure of sensitivity to binaural TFS. The aim of this study was to improve speech in noise perception with fast transition consonant vowel words (VCV) and identify interaural phase difference (IPD) which TFS-LF is more appropriate. TFS-LF were performed in three frequencies, 250, 500 and 750 Hz
^15^. 

Signal-To-Noise Ratio (SNR) 50% is used routinely by audiology clinics. Age related hearing loss have decline speech discrimination ability in similar SNR compare to normal hearing ability and require higher SNR
^23^.

Several test and questionnaire are performed to assess the ability to hear and process sounds and speech from different locations which called spatial hearing speech. In this study we use The Speech, Spatial and Qualities of Hearing Scale (SSQ).

The validity of TFS-LF, SNR 50% and SSQ questionnaire to recognise hearing loss have been confirmed previously
^15,
22,
23^.

We designed stimulus software which divided sound signal to envelope (ENV) and TFS. In this program ENV is removed and only TFS is preserved.

In conclusion in this study, we will attempt to prove by special rehabilitation training based on TFS damage age-related hearing loss can be improved.

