### Speech stimulus process

The TFS speech consists of single syllable recorded in / a / C / a / with various 16 consonant format which included Aja, Aka, Ara,…. and it is pronounced by a native-speaking man. The analogue signals are converted to digital a 16-bit at 44.1 KHz sampling frequency. The stimulus synthesis process is performed in MATLAB software and the software is provided in C programming language.

The original bandpass is filtered into 16 bands of equal bandwidth on a log frequency scale spanning 80 to 8020 Hz. Each Bandpass signal is decomposed to ENV and TFS by Hilbert transform. The ENV component is discarded and TFS component is normalized and TFS component in each band summed lastly creating TFS speech.

After rehabilitation, the SNR (50%) using the WIN test, and a binaural TFS test and SSQ questionnaire will be evaluated again in intervention group. Results will be compared in intervention and control groups before and after the rehabilitation program.

***Outcomes***.
*SNR (50%):* single syllable words in the presence of noise at different signal-to-noise ratios (0, + 4, + 8, + 12, + 16, + 20, + 24) as binaural in two study groups and compare the SNR (50%). Differences in scores before and after rehabilitation training between the two groups will be compared.

The Words-in-Noise (WIN) materials were developed to evaluate the ability of listeners to understand words in multitalker babble. The WIN involves in which the level of the noise is fixed and five words are presented at seven signal-to-noise ratios from 24 to 0 dB in 4 dB decrements. The 35 words are spoken by a native male speaker. The metric of interest is the signal-to-noise ratio (S/N) at which recognition performance is 50%, which is a value determined with the Spearman Karber equation see (
*Extended data:* S2).

Binaural TFS test: determines the binaural change of phase difference at different frequencies in intervention and control groups before and after rehabilitation training.

The correlation between the results of speech perception test scores in the presence of noise with the results of binaural TFS test in the two groups after rehabilitation program will be assessed.

*SSQ questionnaire score:* provided to each group before and after rehabilitation training. Scores between intervention and control groups will be compared (
*Extended data:* S3).

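### The protocol contradicts itself on whether controls are retested; if only the intervention group is retested, the between-group comparison cannot be computed

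*Protocol article*

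**What the plan says.** Two places limit the retest to one arm.

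- The Discussion does so explicitly, of the TFS test, SNR (50%) and the SSQ: "They are performed in both intervention and control group but at the end of study we measure only the tests in intervention population".
- The procedures text in Speech stimulus process does so by naming one group: "After rehabilitation, the SNR (50%) using the WIN test, and a binaural TFS test and SSQ questionnaire will be evaluated again in intervention group".

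The rest of Speech stimulus process, including its Outcomes part, describes a two-arm retest.

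- General, in the sentence straight after the one just quoted: "Results will be compared in intervention and control groups before and after the rehabilitation program".
- SNR (50%): "Differences in scores before and after rehabilitation training between the two groups will be compared".
- Binaural TFS test: phase differences are determined "in intervention and control groups before and after rehabilitation training".
- SSQ: "provided to each group before and after rehabilitation training".
- The correlation of speech-in-noise results with binaural TFS results "in the two groups after rehabilitation program will be assessed".

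The Abstract places the three tests at the start and end of the study without limiting them to one arm. Statistical analysis names the paired t-test and analysis of covariance, to be used as circumstances dictate. Study design describes 1:1 randomisation with a control group that receives no programme, and the Sample size text uses a formula for two independent groups.

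**The concern.** Who is measured at the end decides what the trial can estimate. A site working from the procedures sentence or the Discussion would not recall the controls, and a missed post-test cannot be recovered afterwards.

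Controls receive no programme, so their second measurement is the only planned guard against changes that would have happened anyway: practice on the word test, familiarity with the TFS task, and the passage of time. Without it, randomisation and the two-group sample size contribute nothing to the effect estimate. The analysis falls back on the paired t-test, which the protocol also lists and which would run without any warning that the control arm is missing.

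**Working it through.** **1. The statements side by side**

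| Place | Outcome | Post-test in controls? |
|---|---|---|
| Discussion | All three | No, explicitly excluded |
| Speech stimulus process, retest sentence | All three | Not named |
| Speech stimulus process, next sentence | Results in general | Yes |
| Outcomes, SNR (50%) | Change between groups | Yes, required |
| Outcomes, binaural TFS | Both groups, both times | Yes |
| Outcomes, SSQ | Both groups, both times | Yes |
| Outcomes, correlation | Post values in both groups | Yes, required |

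The Discussion sentence sets both groups at baseline against one group at the end, so it cannot be squared with the Outcomes.

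**2. What cannot be computed under the restriction**

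The planned contrast for SNR (50%) is

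(mean post − mean pre) in the intervention arm − (mean post − mean pre) in the control arm.

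With no control post scores, the second bracket does not exist. An ANCOVA, post = a + b × baseline + τ × arm, fails for the same reason: every participant with a post score has the same value of arm, so τ cannot be separated from the intercept. What is left is the mean change in the intervention arm, whose expectation is training effect + drift.

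**3. The plan's own sample size**

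The protocol states 15 per group, allowing for 20% dropout. The dropout step fits 12 analysable per group: 12 / (1 − 0.20) = 15. The means and SDs are not given, so 12 cannot be derived independently. Back-solving the stated formula with equal SDs, d = √(2/12) × (1.960 + z for power):

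- 80% power: 0.408 × (1.960 + 0.842) = 1.14
- 85% power: 0.408 × (1.960 + 1.036) = 1.22

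Both powers are shown because the protocol lists 80% among the formula inputs and 85% in the text. I therefore use 12 and 15 as the range of participants with post data in one arm.

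**4. Size of the problem if only the intervention arm is retested**

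Assumption: training has no effect, and scores shift on retest by δ SDs of the change score. No document gives δ, so a range from zero is shown. For a two-sided 5% paired t-test, the rejection rate comes from the noncentral t distribution with n − 1 degrees of freedom and noncentrality δ√n. For example, δ = 0.5 gives 0.5 × √12 = 1.73 and 0.5 × √15 = 1.94.

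| Drift δ (SD of change) | n = 12 | n = 15 |
|---|---|---|
| 0 | 5% | 5% |
| 0.25 | 12% | 15% |
| 0.5 | 35% | 44% |
| 0.75 | 66% | 77% |
| 1.0 | 88% | 95% |

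**5. After the fix**

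If both arms are retested alike, a drift common to both cancels from the contrast. With 12 per arm, the normal approximation gives 80% power at d = 1.14 and 85% at d = 1.22 (76% and 82% with the t distribution). Adding the control retest does not change N.

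**The case against.** A reader might infer from the Discussion that the sponsor has decided against retesting controls, so that this is in effect a single-arm before-after study. The documents do not support that.

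- Only the Discussion contains an explicit exclusion, in one loosely worded narrative sentence. The procedures sentence names the intervention group but does not exclude controls, and the next sentence promises a comparison of both groups before and after.
- Every outcome, the sample size formula and the mention of ANCOVA fit a two-arm retest, and the Abstract does not restrict the final tests.
- The schematic of procedures and timeline (Extended data, Figure S1) is not available here and may show who is retested.

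These points stand, and they make this an internal inconsistency and not an established design choice. They do not remove it: the sentences that say who is tested conflict with those that say what is compared, and a figure held elsewhere would not correct the text.

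Two further limits apply. The rejection rates rest on an assumed drift: at zero drift there is no inflation, and at 0.25 SD it is modest. It is also tempting to add regression to the mean to the list of biases. Entry is by a yes/no complaint and audiometry, not by an extreme WIN, TFS-LF or SSQ score, so that mechanism has little support here, though it is plausible for the self-reported SSQ. Practice, familiarity and time effects are enough for the argument.

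**Conclusion.** The protocol is wrong as written, because it gives incompatible accounts of whether controls have a post-test on all three outcomes. That finding needs no assumption.

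The consequence is conditional. If the restriction is followed, the randomised comparison is lost entirely, and a retest effect of moderate size would often be read as benefit: 35–44% false positives at an assumed 0.5 SD of the change score, within a range of 5% at no drift to 66–77% at 0.75 SD. These figures also assume that the lone paired t-test is the analysis used. If the Outcomes are followed, the comparison can be computed at the planned size.

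It must be settled before the final tests. Study status places allocation in the future, although Study design reports it in the past tense, and the protocol says that no further modifications are planned. The conflict will therefore stand unless it is raised.

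**What to change.** - In Speech stimulus process, reword the retest sentence so that all randomised participants in both arms repeat WIN SNR (50%), TFS-LF (250, 500 and 750 Hz) and the SSQ at the same interval after baseline, set to coincide with the end of the five-week programme, and under the same test conditions.
- In the Discussion, delete the clause that limits the final tests to the intervention population, and say the same as the amended procedures.
- In Statistical analysis, name the between-group comparison as the main analysis, for example ANCOVA on the post score adjusted for baseline, which the section already mentions. Keep the paired t-test as a within-group description only.
- Check that Extended data Figure S1 agrees.

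The cost is one repeat test visit for about 15 controls with tests already in use, which the Outcomes already imply, plus a few amended sentences. N does not change. If the final visits have already passed without a control retest, this repair is no longer available, and the results should be reported as an uncontrolled before-after change.

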### Statistical analysis

In descriptive analysis of data, central tendency and dispersion indices (mean, median and standard deviation) will be used. Kolmogorov–Smirnov test will be used to test whether two random samples are drawn from the same normal distribution. Otherwise its nonparametric equivalent will be used. Depending on the circumstances, paired t-test and analysis of covariance will be used to compare pre- and post-rehabilitation program. Other analytical tests will be used as required during the data processing phase. SPSS software (V20.0, IBM Corporation, New York, USA) will be used for statistical data analysis and the significance level for all tests will be 0.05.

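### Two sentences confine the end-of-study tests to the trained arm, although the Outcomes text, the sample size and the abstract need or imply testing in both arms

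*Protocol article*

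**What the plan says.** All references are to the protocol article.

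Two places point to a post-test in the trained arm only:

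- **Discussion.** After naming the TFS test, SNR 50% and SSQ, it says they are carried out in both groups but that "at the end of study we measure only the tests in intervention population".
- **Speech stimulus process**, paragraph before Outcomes. After rehabilitation, the same three measures "will be evaluated again in intervention group". Controls are not mentioned. For the pre-training tests, by contrast, Study procedures speaks of all participants.

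The rest of the text needs or implies a post-test in both arms:

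- **The next sentence in Speech stimulus process:** "Results will be compared in intervention and control groups before and after the rehabilitation program".
- **Outcomes, SNR (50%):** "Differences in scores before and after rehabilitation training between the two groups will be compared".
- **Outcomes, binaural TFS:** phase-difference results "in intervention and control groups before and after rehabilitation training".
- **Outcomes, correlation of speech-in-noise with TFS:** "in the two groups after rehabilitation program will be assessed".
- **Outcomes, SSQ:** "provided to each group before and after rehabilitation training".
- **Statistical analysis:** "paired t-test and analysis of covariance will be used to compare pre- and post-rehabilitation program".
- **Sample size:** a formula for two independent groups, giving 15 per group.
- **Abstract:** tests at the start and end of the study, with no restriction by arm.

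**The concern.** Controls receive no training (Study design). Their change over the five weeks is what separates a training effect from familiarity with the tests and the passage of time. That separation requires the controls to be tested twice.

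If staff follow the Discussion sentence, or read the procedural sentence literally, controls are not recalled. The trial then has randomised arms but no randomised comparison of the outcome. The comparison of change promised under Outcomes has no control data, and an analysis of covariance on post-test scores has no control outcomes from which to estimate an arm effect. What remains is a before-after test in the trained arm, which cannot tell training from retesting. Comparing trained post-tests with control baselines would not help, because the retest gain would sit in one arm only.

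**Working it through.** **1. The plan's own figure.** Sample size gives 15 per group after allowing for 20% drop-out. No means or standard deviations are stated, so the formula cannot be run forward. The drop-out step is consistent: 12 / (1 − 0.20) = 15. The working numbers are therefore 15 per arm at entry and about 12 evaluable.

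**2. Control post-tests that each planned analysis needs.**

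| Planned analysis | Needs control post-test? | Available under the Discussion sentence |
|---|---|---|
| SNR (50%): change compared between groups | Yes | 0 of 15 |
| Binaural TFS: both groups before and after | Yes | 0 of 15 |
| Correlation in both groups after the programme | Yes | 0 of 15 |
| SSQ: each group before and after | Yes | 0 of 15 |
| Analysis of covariance with an arm effect | Yes | 0 of 15 |
| Paired t-test within the trained arm | No | feasible |

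Only the last row survives. With control post-tests, the between-arm comparison keeps about 12 + 12 participants.

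**3. What the surviving test would do (illustration).** Suppose training has no effect and retesting alone shifts scores by *d* standard deviations of the change score. The document gives no retest figure, so *d* is assumed over a range. The paired t statistic then follows a noncentral t distribution:

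- degrees of freedom = n − 1
- noncentrality = d × √n (for n = 15 and d = 0.5: 0.5 × 3.873 = 1.94)
- rejection rate = P(|T| > t(0.975, n − 1)), two-sided 0.05

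| Assumed d | n = 15 | n = 12 |
|---|---|---|
| 0 | 5% | 5% |
| 0.25 | 15% | 12% |
| 0.50 | 44% | 35% |
| 0.75 | 77% | 66% |

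Simulation with 200,000 runs agrees: 0.148, 0.438 and 0.772 for n = 15, and 0.122, 0.353 and 0.657 for n = 12, at d = 0.25, 0.5 and 0.75.

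**4. The same shift with both arms retested.** A shift common to both arms cancels in the difference of mean changes, so the two-arm test keeps its nominal level. Simulated at d = 0.5, the rejection rate is 0.049 with 15 per arm and 0.050 with 12 per arm.

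**The case against.** The strongest reply is that this is loose wording. Every outcome definition involves control post-tests, the sample size assumes two groups, and the abstract sets testing at the beginning and end for everyone. Against that stands one poorly worded Discussion sentence. The sentence under Speech stimulus process does not contain the word only, and the sentence after it compares both groups before and after. Much of this stands: the weight of the text favours testing both arms, and only the Discussion sentence excludes controls explicitly. The reply does not remove the conflict. The explicit exclusion is in the current text, the procedural sentence leans the same way, and nothing reconciles them with the outcome definitions.

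A second reply is that the rejection rates are doubly conditional: on the less-supported reading being carried out, and on a retest gain nobody has stated. That is correct. They show what would be lost. They do not estimate an error in this trial, and the contradiction does not depend on them.

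Two further inferences are tempting but not supported:

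- **That the controls' retest has no timing.** The abstract places testing at the end of the study without limit by arm, and the timeline is in Figure S1 of the extended data, which is not shown.
- **That flexible sessions and duration (Study design) contradict the five weeks.** The Discussion explains that the schedule is three times weekly for five weeks for everyone and that the time per session varies.

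**Conclusion.** The point holds as an internal contradiction about who is tested at the end. The Discussion explicitly leaves controls out and one procedural sentence names only the trained arm, while the outcome definitions, the sample-size basis and the abstract point the other way.

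A reader might infer that the trial was deliberately designed with a one-arm post-test. The documents do not support that; the intended plan is more likely both arms. The consequence is therefore conditional. If the Discussion sentence is followed, all 15 control post-tests are lost on all three outcomes, and with them the randomised comparison. The trained-arm test would then have a false-positive rate that rises with any retest gain, to 44% with 15 participants (35% with 12) at an assumed gain of half an SD of change. If both arms are tested as Outcomes implies, nothing is lost and only the text needs correcting. It should be corrected, because the error is cheap to remove and cannot be repaired once the end-of-study visits have passed.

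**What to change.** Correct the Discussion sentence and the matching sentence under Speech stimulus process. Both should state that WIN SNR (50%), TFS-LF and SSQ are repeated at the end of the five-week period in the intervention and control arms alike, and that the effect of training is judged on the between-arm comparison. A within-arm paired test can be kept as description.

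The cost is two sentences and, if not already planned, one end-of-study visit for each of the 15 controls. The sample size does not change. The article is unclear on whether allocation has happened: Study status puts it in the near future, while Study design uses the past tense. The correction works either way, provided the control end-of-study visits can still be held.
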